## 18.0 **MASTER FORMS SET**

- 18.1 The Model Informed Consent Form is included in this section, preceded by "Notes for Local Institution Consent Form Authors" and "Notes for Local Investigators." The study - as well as the local consent form meeting the guidelines noted in these documents - must be reviewed and approved by the Institutional Review Board prior to registration and treatment of patients on this study.
- 18.2 This section includes copies of all data forms which must be completed for this study. These include:
- a. **S1200** Registration Worksheet (Form #39748)
  - b. **S1200** Prestudy Form (Form #41314)
  - c. **S1200** Cover Sheet for Patient-Completed Questionnaires (Form #19445)
  - d. **S1200** Brief Pain Inventory Short Form (BPI-SF) (Form #40963)
  - e. **S1200** Western Ontario and McMaster Universities Osteoarthritis (WOMAC) Index (Version 3.1) (Form #33579)
  - f. **S1200** Modified-Score for the Assessment and Quantification of Chronic Rheumatoid Affections of the Hands (M-SACRAH) (Form #48347)
  - g. **S1200** PROMIS Pain Impact-Short Form (PROMIS PI-SF) (Form #28494)
  - h. **S1200** FACT-ES Trial Outcome Index (Version 4) (Form #13659)
  - i. **S1200** Aromatase Inhibitor Usage Form (Form #39879)
  - j. **S1200** Functional Testing (Form #37709)
  - k. **S1200** Adherence to Acupuncture Form (Form #6044)
  - l. **S1200** Adverse Event Summary Form (Form #5183)
  - m. **S1200** Supplemental Agents Reporting Form (Form #9413)
  - n. **S1200** Assessment of Blinding (Form #20574)
  - o. **S1200** Off Protocol Notice (Form #9707)
  - p. Follow-Up Form (Form #64587)
  - q. Notice of Death (Form #49467)

**DRAFT****SWOG  
S1200 REGISTRATION WORKSHEET**

Page 1 of 1

**RANDOMIZED BLINDED SHAM- AND WAITLIST-CONTROLLED TRIAL  
OF ACUPUNCTURE FOR JOINT SYMPTOMS RELATED TO AROMATASE  
INHIBITORS IN WOMEN WITH EARLY STAGE BREAST CANCER**

Activation Date

Last Amended Date

Registration Step **1**

**INSTRUCTIONS:** All of the information on this Registration Worksheet and the Protocol Eligibility Section must be answered appropriately for a patient to be considered eligible for registration. This Registration Worksheet must be entirely filled out and referred to during the registration. **Do NOT submit this worksheet as part of the patient data.**

**SWOG PATIENT ID**

If the patient has a SWOG Patient ID assigned by a prior registration or Specimen Tracking, choose "Previous Patient" and use that number.

SWOG Patient ID Status: ☐ New Patient☐ Previous Patient:SWOG Patient ID: **DEMOGRAPHY**

Full names preferred, initials OK

Patient First Name: Patient Middle Name: Patient Last Name: **FOR SWOG INSTITUTIONS**Registrar's SWOG Roster ID Number: SWOG Investigator Number: SWOG Treating Institution Number: **PATIENT INFORMATION**Date Informed Consent Signed:  /  / Date HIPAA Authorization signed:  /  /  (Not required if Country of Residence is not USA)Projected Start Date of Treatment:  /  / **Stratification Question**

Study Site: ☐ (1) Columbia U ☐ (2) FHCRC ☐ (3) Grand Rapids CCOP ☐ (4) Kaiser Permanente NoCa  
☐ (5) Oregon HSU ☐ (6) USC

**Indicate how the patient answered the following questions on the consent form**

My specimens may be kept for use in research to learn about, prevent, treat, or cure cancer.

☐ Yes ☐ No

My specimens may be kept for use in research about other health problems (for example: diabetes, Alzheimer's disease, or heart disease).

☐ Yes ☐ No

Someone may contact me in the future to ask me to allow other uses of my specimens.

☐ Yes ☐ No

I agree to allow my study doctor, or someone approved by my study doctor, to contact me regarding future research involving my participation in this study.

☐ Yes ☐ No**Patient Eligibility**

Has the SWOG Registration Worksheet been completed entirely and is the patient eligible according to the current version of protocol section 5.0?

☐ Yes ☐ No

Draft

1/6/2012

**DRAFT****SWOG  
S1200 PRESTUDY FORM**

Page 1 of 2

SWOG Patient ID SWOG Study No. S1200Registration Step 1

Patient Initials \_\_\_\_\_ (L, F M)

Institution / Affiliate \_\_\_\_\_ Physician \_\_\_\_\_

**Instructions:** Submit this form within 7 days of registration. All dates are **MONTH, DAY, YEAR**. Explain any blank fields or blank dates in the **Comments** section. Place an ☒ in appropriate boxes. Circle **AMENDED** items in red and write **AMENDED** across top of form.

**ELIGIBILITY VERIFICATION:**

Each of the fields below corresponds to a criterion in Section 5 and must be completed for patient to be eligible.

**PATIENT AND DISEASE DESCRIPTION**Performance Status: ☐ 0 ☐ 1 Height:  cm Weight:  kgDate of initial diagnosis of breast cancer:  /  / Stage of breast cancer (select one): ☐ I ☐ II ☐ IIITumor Laterality (select one): ☐ Left ☐ Right ☐ Bilateral

Prior surgery (select one):

☐ Modified radical mastectomy, date:  /  / ☐ Breast sparing surgery, date:  /  / **RECEPTOR STATUS** (Use institutional standards; borderline results should be reported as positive.)ER Status: ☐ ER- ☐ ER+PgR Status: ☐ PgR- ☐ PgR+HER-2/neu status: ☐ HER2+ ☐ HER2- ☐ Equivocal ☐ Not doneSpontaneous menstrual bleeding within the last 12 months? ☐ Yes ☐ NoMonth and year of last menstrual period:  / Current GnRH agonist? ☐ Yes ☐ NoDate started:  /  / Hysterectomy? ☐ Yes ☐ NoBilateral oophorectomy? ☐ Yes ☐ No ☐ UnknownSerum FSH: .  IU/L Date FSH obtained:  /  / Institutional post-menopausal range: .  IU/L - .  IU/L*continued on next page*

11/29/2011

Draft

**DRAFT****SWOG  
S1200 PRESTUDY FORM**

Page 2 of 2

SWOG Patient ID SWOG Study No. S1200Registration Step 1

Patient Initials \_\_\_\_\_ (L, F M)

**ADDITIONAL PRESTUDY DATA:**Has the patient ever had acupuncture treatment? ☐ Yes ☐ No

If Yes, reason: \_\_\_\_\_

Date of last treatment: //Does the patient have a severe bleeding disorder? ☐ Yes ☐ NoIs the patient right- or left-handed? (select one) ☐ Right-handed ☐ Left-handed ☐ Ambidextrous

Has the patient's joint pain/stiffness recorded on the Brief Pain Inventory (select one):

☐ started after initiating aromatase inhibitor therapy☐ worsened after initiating aromatase inhibitor therapy**PRIOR TREATMENT RELATED TO THIS CANCER**

Prior Therapy Type(s) (select all that apply):

☐ Aromatase Inhibitor Date started: //

Type of Aromatase Inhibitor:

☐ Anastrozole/Arimadex☐ Letrozole/Femara☐ Exemestane/Aromasin☐ Bisphosphonate Date started: //☐ Tamoxifen/Nolvadex☐ Chemotherapy☐ Radiation therapyHas the patient received prior taxane therapy for any reason? ☐ Yes ☐ No**Comorbid Conditions**☐ Renal insufficiency☐ Abnormal pulmonary function☐ Hypertension☐ Heart disease☐ Hearing impairment☐ Visual impairment☐ Deformity or orthopedic impairment☐ Diminished mental capacity/neurologic impairment/dementia☐ Arthritis☐ HIV/AIDS☐ Other comorbidities (please specify): \_\_\_\_\_

Comments:

11/29/2011

Draft

[figure not shown]

**DRAFT****SWOG**

Page 1 of 1

**S1200 COVER SHEET FOR PATIENT-COMPLETED QUESTIONNAIRES**SWOG Patient ID SWOG Study No. Registration Step 

Patient Initials \_\_\_\_\_ (L, F M)

Date Form Completed:  /  / 

Institution / Affiliate \_\_\_\_\_ Physician \_\_\_\_\_

**Planned Assessment:**☐ Baseline ☐ 6-week visit ☐ 12-week visit ☐ 16-week contact ☐ 20-week contact  
☐ 24-week visit ☐ 52-week visit

**Instructions:** Please complete form at time of registration and at 6 weeks, 12 weeks, 16 weeks, 20 weeks, 24 weeks, and 52 weeks post-registration. **Note: The prestudy baseline Brief Pain Inventory Short Form is an eligibility requirement and must be completed within 14 days prior to registration. All other baseline forms must be completed prior to initiation of acupuncture treatment.** All dates are **MONTH, DAY, YEAR**. Place an **X** in appropriate boxes. Circle **AMENDED** items in red and write **AMENDED** across the top of this form or any of the attached patient-completed forms.

Was the Brief Pain Inventory Short Form (BPI-SF) completed? ☐ No ☐ YesWas the WOMAC Index completed? ☐ No ☐ YesWas the M-SACRAH completed? ☐ No ☐ YesWas the PROMIS PI-SF completed? ☐ No ☐ YesWas the FACT-ES Trial Outcome Index completed? ☐ No ☐ YesWas the Aromatase Inhibitor Usage Form completed? ☐ No ☐ YesWas the S1200 Assessment of Blinding Form completed? ☐ No ☐ Yes

If any of the questionnaires was completed:

Did the patient require any assistance in completing the questionnaire(s)? ☐ No ☐ Yes

If Yes, Describe: \_\_\_\_\_

**Method of completing questionnaire(s):**☐ In the clinic  
☐ By telephone  
☐ Other (Please specify): \_\_\_\_\_

If not completed, please give reason (select one):

☐ Illness/deteriorating health  
☐ Not illness related (e.g., unable to contact, patient refusal, patient failure to return questionnaire)  
☐ Institution error (e.g., forgot to administer, did not continue schedule when patient went off treatment)  
☐ Death  
☐ Other  
\_\_\_\_\_

I have reviewed the Cover Sheet and Questionnaire(s). All forms are complete or an explanation is given for any missing data.

Person completing form,  
last name: \_\_\_\_\_Person completing  
form, phone: (  )  - **Comments:**

11/29/2011

Draft

**DRAFT****SWOG**  
**S1200 BRIEF PAIN INVENTORY SHORT FORM (BPI-SF)**

|                                                                                                                                                                                                                                                                                                              |                                                                                        |                                        |
|--------------------------------------------------------------------------------------------------------------------------------------------------------------------------------------------------------------------------------------------------------------------------------------------------------------|----------------------------------------------------------------------------------------|----------------------------------------|
| SWOG Patient ID                                                                                                                                                                                                                                                                          | SWOG Study No.                                                     | Registration Step  |
| Patient Initials _____ (L, F M)                                                                                                                                                                                                                                                                              | Date of Completion:  /  /  |                                        |
| Planned Assessment:  Prestudy  6-week visit  12-week visit  16-week contact
 20-week contact  24-week visit  52-week visit |                                                                                        |                                        |
| Institution/Affiliate _____                                                                                                                                                                                                                                                                                  |                                                                                        | Physician _____                        |

**Instructions:** You will be asked to fill out this form at the times listed above for a total of 7 times. The staff at your clinic will remind you of the times the questionnaire is to be completed. For each item below, please put an ☒ in the one box that best describes your joint pain (page 1) and how that pain affects your daily activities (page 2). Be sure to read each question carefully and to provide one answer for each question. Thank you for participating in this study.

1. Throughout our lives, most of us have had pain from time to time (such as minor headaches, sprains, and toothaches). Have you had joint pain other than these everyday kinds of pain in the last week?

☐ Yes ☐ No

2. Please rate your joint pain by selecting the one number that best describes your joint pain at its WORST in the last week.

☐ 0 ☐ 1 ☐ 2 ☐ 3 ☐ 4 ☐ 5 ☐ 6 ☐ 7 ☐ 8 ☐ 9 ☐ 10  
No pain Pain as bad as you can imagine

3. Please rate your joint pain by selecting the one number that best describes your joint pain at its LEAST in the last week.

☐ 0 ☐ 1 ☐ 2 ☐ 3 ☐ 4 ☐ 5 ☐ 6 ☐ 7 ☐ 8 ☐ 9 ☐ 10  
No pain Pain as bad as you can imagine

4. Please rate your joint pain by selecting the one number that best describes your joint pain on the AVERAGE.

☐ 0 ☐ 1 ☐ 2 ☐ 3 ☐ 4 ☐ 5 ☐ 6 ☐ 7 ☐ 8 ☐ 9 ☐ 10  
No pain Pain as bad as you can imagine

5. Please rate your joint pain by selecting the one number that tells how much joint pain you have RIGHT NOW.

☐ 0 ☐ 1 ☐ 2 ☐ 3 ☐ 4 ☐ 5 ☐ 6 ☐ 7 ☐ 8 ☐ 9 ☐ 10  
No pain Pain as bad as you can imagine

6. Are you taking any oral medications for your joint pain? ☐ Yes ☐ No

7. In the last week, how much RELIEF have joint pain treatments or medications provided? Please select the percentage that most shows how much.

☐ 0% ☐ 10% ☐ 20% ☐ 30% ☐ 40% ☐ 50% ☐ 60% ☐ 70% ☐ 80% ☐ 90% ☐ 100%  
No relief Complete relief

*continued on next page*

[figure not shown]

**SWOG**  
**S1200 BRIEF PAIN INVENTORY SHORT FORM (BPI-SF)**SWOG Patient ID SWOG Study No. Registration Step 

Patient Initials \_\_\_\_\_ (L, F M)

Date of Completion:  /  / 

**Planned Assessment:** ☐ Prestudy ☐ 6-week visit ☐ 12-week visit ☐ 16-week contact  
☐ 20-week contact ☐ 24-week visit ☐ 52-week visit

*...Continued from Page 1***Select the one number that describes how, during the last week, JOINT PAIN HAS INTERFERED with your:****8. General Activity**

☐ 0 ☐ 1 ☐ 2 ☐ 3 ☐ 4 ☐ 5 ☐ 6 ☐ 7 ☐ 8 ☐ 9 ☐ 10  
Does not interfere Completely interferes

**9. Mood**

☐ 0 ☐ 1 ☐ 2 ☐ 3 ☐ 4 ☐ 5 ☐ 6 ☐ 7 ☐ 8 ☐ 9 ☐ 10  
Does not interfere Completely interferes

**10. Walking ability**

☐ 0 ☐ 1 ☐ 2 ☐ 3 ☐ 4 ☐ 5 ☐ 6 ☐ 7 ☐ 8 ☐ 9 ☐ 10  
Does not interfere Completely interferes

**11. Normal work (includes both work outside the home and housework)**

☐ 0 ☐ 1 ☐ 2 ☐ 3 ☐ 4 ☐ 5 ☐ 6 ☐ 7 ☐ 8 ☐ 9 ☐ 10  
Does not interfere Completely interferes

**12. Relations with other people**

☐ 0 ☐ 1 ☐ 2 ☐ 3 ☐ 4 ☐ 5 ☐ 6 ☐ 7 ☐ 8 ☐ 9 ☐ 10  
Does not interfere Completely interferes

**13. Sleep**

☐ 0 ☐ 1 ☐ 2 ☐ 3 ☐ 4 ☐ 5 ☐ 6 ☐ 7 ☐ 8 ☐ 9 ☐ 10  
Does not interfere Completely interferes

**14. Enjoyment of life**

☐ 0 ☐ 1 ☐ 2 ☐ 3 ☐ 4 ☐ 5 ☐ 6 ☐ 7 ☐ 8 ☐ 9 ☐ 10  
Does not interfere Completely interferes

Source: Brief Pain Inventory-Short Form: C. S. Cleeland, PhD, University of Texas, M. D. Anderson Cancer Center, Houston, TX (Cleeland, 1994)

*continued on next page*[figure not shown]

**DRAFT****SWOG****S1200 BRIEF PAIN INVENTORY SHORT FORM (BPI-SF)**SWOG Patient ID SWOG Study No. Registration Step 

Patient Initials \_\_\_\_\_ (L, F M)

Date of Completion:  /  / 

**Planned Assessment:** ☐ Prestudy ☐ 6-week visit ☐ 12-week visit ☐ 16-week contact  
☐ 20-week contact ☐ 24-week visit ☐ 52-week visit

**Instructions:** In the first two questions on page 1 of this form, you were asked about joint pain. The two questions below ask instead about joint stiffness. For each item below, please put an ☒ in the one box that best describes your joint stiffness. Be sure to read each question carefully and to provide one answer.

**15. Throughout our lives, most of us have had stiffness from time to time (such as difficulty getting up from a chair). Have you had joint stiffness in the last week?**

☐ Yes ☐ No

**16. Please rate your joint stiffness by selecting the one number that best describes your joint stiffness at its WORST in the last week.**

☐ 0 ☐ 1 ☐ 2 ☐ 3 ☐ 4 ☐ 5 ☐ 6 ☐ 7 ☐ 8 ☐ 9 ☐ 10  
No stiffness Stiffness as bad as you can imagine

Draft

2/9/2012

### S1200 WESTERN ONTARIO AND MCMASTER UNIVERSITIES OSTEOARTHRITIS (WOMAC) INDEX (VERSION 3.1)

SWOG Patient ID

SWOG Study No.  S  1  2  0  0

Registration Step  1

Patient Initials \_\_\_\_\_ (L, F M)

Date of Completion:   /   /

Planned Assessment: ☐ Baseline ☐ 6-week visit ☐ 12-week visit ☐ 24-week visit ☐ 52-week visit

Institution/Affiliate \_\_\_\_\_ Physician \_\_\_\_\_

**Instructions:** You will be asked to complete this form at time of registration and at 6 weeks, 12 weeks, 24 weeks, and 52 weeks post-registration. All dates are **MONTH, DAY, YEAR**. Thank you for your participation on this study.

#### Section A: PAIN

Think about the pain you felt during the past week caused by your joints. For each of the following questions, select the number between "0" and "10" that best describes the amount of **pain** you have experienced by putting an ☒ in the box next to that number.

Question: **How much pain have you had...**

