related arthralgia. Subsequently, 53 patients who were initiating AI therapy were prospectively evaluated. Compared to baseline, there was a 49% increase in joint pain severity at 6 months and an 86% increase in pain-related interference at 6 months as assessed by the Brief Pain Inventory-Short Form (BPI-SF). At 3 months, 46% of subjects had at least a 2-point increase in the BPI-SF worst pain score (0-10 scale) from baseline, and at 6 months, a significant decrease in pinch grip strength was detected ( $p=0.05$ ). (19) The results are consistent with findings from other studies. (16, 20)

In a study evaluating menopausal symptoms in breast cancer patients receiving endocrine therapy, there was a significant change in musculoskeletal pain in women receiving AIs. (21) Fifty percent of women who were asymptomatic at baseline reported variable degrees of pain after one month of treatment. There was a marked increase in the number of patients reporting severe to intolerable symptoms after three months of therapy, which led to treatment interruption in 11% of patients. Patients usually present with polyarthralgia affecting the hands, knees, hips, lower back or shoulders, which is often refractory to conventional pharmacological interventions. (16) The musculoskeletal pain appears to be specific for this class of compounds, regardless of the AI prescribed.

Recent studies have found that AI-induced arthralgia is accompanied by physical changes in the affected joints seen on MRI, EMG, and ultrasound. Women on AIs for six months had decreased grip strength and increased tenosynovial changes seen on MRI. (22) In a study conducted by Dizdar et al., women taking AIs have increased tendon thickness and higher rates of effusions in hand joints/tendons on musculoskeletal sonography compared to women who never received AIs. (23) AI use is also associated with a greater incidence of carpal tunnel syndrome of moderate intensity and short duration. (24)

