Since there are no well-validated measures specifically for AI-induced arthralgias, scales that captured joint pain, stiffness, and functional status in the hips and knees (WOMAC) and hands (M-SACRAH) were selected, and a general pain scale used in cancer patients (BPI-SF). The BPI-SF (137) is a 14-item questionnaire which asks patients to rate pain over the prior week and the degree to which it interferes with activities on a 0 to 10 scale. Numeric rating scales such as the BPI are among the most common, valid, and reliable measures used to assess cancer pain. (138) The Western Ontario and McMaster Universities Osteoarthritis Index (WOMAC) Version 3.1 is a validated measure for assessing osteoarthritis of the knees or hips and consists of 24 questions related to three subscales: pain, stiffness, and physical function. (139) The Modified-Score for the Assessment and Quantification of Chronic Rheumatoid Affections of the Hands (M-SACRAH) consists of three domains assessing pain, stiffness, and functional status in patients suffering

from hand osteoarthritis and rheumatoid arthritis. (140) Well-validated quantitative functional testing with grip strength to assess hand function and the “Timed Get Up and Go” (TGUG) test to assess functional status in the lower extremities have also been included. (141,142)

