### Acupuncture for Aromatase Inhibitor-Related Arthralgias

Researchers at CUMC have extensive experience evaluating interventions for the treatment of AI-induced arthralgias. Since research in this area is limited, a small pilot study evaluating the use of acupuncture to relieve symptoms of AI-associated arthralgias was initially conducted. In this study of 21 women treated with full body and auricular acupuncture twice weekly for six weeks, improvements were reported in pain severity, pain-related functional outcomes, and physical well-being, and no significant adverse events were reported. (79) Another pilot study used electro-acupuncture administered twice weekly for 2 weeks followed by 6 weekly treatments in 12 breast cancer survivors with AI-related arthralgia. (143) Similarly, the patients reported significant reductions in pain severity, stiffness, and joint symptom interference according to the BPI. Subjects also reported a significant decrease in fatigue and anxiety. These studies were limited due to small sample sizes, unblinded interventions, and lack of an adequate control group.

A randomized, blinded, sham-controlled study in 38 women with early stage breast cancer and AI-induced arthralgias to assess the efficacy of acupuncture was then conducted. As is shown in Figure 1, a 6-week course of true acupuncture was associated with about a 50% decrease in mean BPI-SF scores. No change from baseline was observed for the sham arm. At 6 weeks, the mean BPI-SF worst pain scores (range, 0-10) were lower for true acupuncture compared to sham acupuncture (3.0 vs. 5.5,  $p<0.001$ ), as well as pain severity (2.6 vs. 4.5,  $p=0.003$ ) and pain-related interference (2.5 vs. 4.5,  $p=0.002$ ). Similar findings were seen for the WOMAC and M-SACRAH scores which assess knee/hip and hand joint symptoms, respectively. (144) These measures were very effective at capturing the symptoms of AI-related arthralgia.

**Figure 1.** Percent change in the group mean Brief Pain Inventory-Short Form (BPI-SF) scores from baseline to 3 and 6 weeks for the true and sham acupuncture groups: A) BPI-SF worst pain, B) BPI-SF pain severity, and C) BPI-SF pain-related interference.

[figure not shown]

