### 10.2 Secondary Endpoints:

To investigate the effects of true acupuncture compared to sham acupuncture and waitlist control on the following outcome measures compared to baseline:

- a. Brief Pain Inventory-Short Form (BPI-SF) worst pain, worst stiffness (items 15 & 16), pain severity, and pain-related interference scores at 6, 12, 16, 20, 24, and 52 weeks.
- b. Western Ontario and McMaster Universities Osteoarthritis (WOMAC) index (pain, stiffness, and function) for the hips and knees at 6, 12, 24, and 52 weeks.
- c. Modified-Score for the Assessment and Quantification of Chronic Rheumatoid Affections of the Hands (M-SACRAH) (pain, stiffness, and function) at 6, 12, 24, and 52 weeks.
- d. PROMIS Pain Impact-Short Form (PROMIS PI-SF) at 6, 12, 24, and 52 weeks.
- e. Quality of life as assessed by the FACT-ES Trial Outcome Index (Version 4) at 6, 12, 24, and 52 weeks.
- f. Functional testing of the hands (grip strength) and legs ('Timed Get Up and Go') at 6, 12, 24, and 52 weeks.
- g. Analgesic and opioid use at 2, 4, 6, 12, 16, 20, 24, and 52 weeks
- h. AI adherence at 12, 24, and 52 weeks.
- i. Urine AI metabolites at 24 and 52 weeks.
- j. Serum hormone biomarkers (estradiol, FSH, LH) and inflammatory biomarkers (serum TNF $\alpha$ , IL-6, IL-12, CRP; urine CTX-II) at 6, 12, and 24 weeks.
- k. Polymorphisms in *CYP19A1*.
- l. Safety and tolerability of acupuncture.

This study will also describe adverse events, assess the association between *CYP19A1* genotype and severity of AI-related joint symptoms, and assess the adequacy of blinding and use of additional off-study acupuncture treatments.

- 10.3 Performance Status: Patients will be graded according to the Zubrod performance status scale.

| POINT | DESCRIPTION                                                                                                                                        |
|--------------|-----------------------------------------------------------------------------------------------------------------------------------------------------------|
| 0            | Fully active, able to carry on all pre-disease performance without restriction.                                                                           |
| 1            | Restricted in physically strenuous activity but ambulatory and able to carry out work of a light or sedentary nature, e.g., light housework, office work. |

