#### Section B: STIFFNESS

Think about the stiffness (not pain) you felt during the past week caused by your joints. Stiffness is a sensation of **decreased** ease in moving your joint. For each of the following questions, select the number between "0" and "10" that best describes the amount of **stiffness** you have experienced by putting an ☒ in the box next to that number.

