#### Section C: DIFFICULTY PERFORMING DAILY ACTIVITIES

Think about the difficulty you had doing the following daily physical activities during the past week caused by your joints. By this we mean **your ability to move around and take care of yourself**. For each of the following questions, select the number between "0" and "10" that best describes the amount of **difficulty** you have experienced by putting an ☒ in the box next to that number.

Question: **How much difficulty have you had...**

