#### DIFFICULTIES IN COPING WITH ACTIVITIES OF DAILY LIFE

Please think of the difficulties you had during the past week in performing the following activities of daily life in view of your **finger joint conditions**. The objective is to **move freely** and to be able to **take care of yourself**. For each question below, please put an ☒ in the box that describes how difficult each activity was for you.

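### The WOMAC is defined as a hip and knee endpoint, but the trial's WOMAC form asks about joints in general, so a WOMAC effect, above all in stiffness, cannot be read as hip/knee-specific

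*Protocol*

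**What the plan says.** Protocol Section 10.2b lists as a secondary endpoint the WOMAC "index (pain, stiffness, and function) for the hips and knees at 6, 12, 24, and 52 weeks". Objective 1.2b uses the same words. The Background gives body site as the reason for having two joint scales: "scales that captured joint pain, stiffness, and functional status in the hips and knees (WOMAC) and hands (M-SACRAH) were selected". It describes the pilot trial's results with the same split: "Similar findings were seen for the WOMAC and M-SACRAH scores which assess knee/hip and hand joint symptoms, respectively".

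The form that patients fill in (Form #33579, Section 18) has three stems:

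- Pain, items 1 to 5: "Think about the pain you felt during the past week caused by your joints".
- Stiffness, items 6 and 7: "Think about the stiffness (not pain) you felt during the past week caused by your joints".
- Function, items 8 to 24: "Think about the difficulty you had doing the following daily physical activities during the past week caused by your joints".

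No stem, item or instruction on the form mentions a hip or a knee. The companion hand form does name its joint. The M-SACRAH asks about difficulties "in view of your finger joint conditions", and its stiffness and pain sections are also tied to the finger joints.

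Appendix 19.2 labels the WOMAC as a hip and knee index and gives its subscale ranges as 0-50, 0-20 and 0-170. It then adds that the scale has also served as a general symptom measure in other musculoskeletal conditions.

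**The concern.** The endpoint names two joints and the question names none. In this population the difference matters. The Background describes "polyarthralgia affecting the hands, knees, hips, lower back or shoulders", and eligibility criterion 5.5 requires a worst joint pain score of at least 5 without saying where. A woman whose pain is in her hands or shoulders can enrol and can answer the WOMAC stems truthfully on the basis of those joints.

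The intervention also treats such joints. Under Appendix 19.1 the joint-specific points are tailored to the patient's most painful joints, and fingers, wrists, shoulders and the lumbar area are among them. Relief at those sites is an intended effect. It can lower the WOMAC score and would then be reported, under 10.2b, as a hip and knee benefit.

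At stake is the anatomical claim attached to a secondary result. The existence of a difference between arms is not in question.

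**Working it through.** **Step 1. Reproduce the plan's figures.** The form scores each item 0 to 10.

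- Pain, items 1-5: 5 × 10 = 50.
- Stiffness, items 6-7: 2 × 10 = 20.
- Function, items 8-24: 17 × 10 = 170.

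All three match the ranges in Appendix 19.2, so the form is the instrument that the endpoint refers to.

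**Step 2. Ask which items restrict the site by their content.** The stems do not restrict it, so only the activity named in an item can. The sorting below is a judgement from the item wording and is not a figure in the protocol.

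| Subscale | Items that do not point to the lower limb | Points open to other joints | Share |
|---|---|---|---|
| Stiffness | 6 (on waking), 7 (after rest) | 2 × 10 = 20 of 20 | 100% |
| Pain | 3 (in bed at night), 4 (sitting or lying) | 2 × 10 = 20 of 50 | 40% |
| Function, narrow reading | 19 (lying in bed), 21 (sitting) | 2 × 10 = 20 of 170 | 12% |
| Function, wide reading | those two plus 15 (shopping), 16 and 18 (socks on and off), 23 and 24 (heavy and light chores) | 7 × 10 = 70 of 170 | 41% |

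The remaining items are walking, stairs, standing, rising, bending, and getting into or out of a car, bed, bath or toilet. A patient would answer these mainly from the legs.

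**Step 3. Look for a restriction elsewhere.** The questionnaire instructions in Section 15.2 do not limit WOMAC answers to any joint. The generalized use noted in Appendix 19.2 does not change the definition in 1.2b or 10.2b, and the same appendix keeps the hip and knee label.

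**Step 4. Ask whether the analysis could repair it.** Neither the Prestudy Form nor the BPI-SF, as shown in Section 18, records which joints hurt. The acupuncturists' record of points used (Section 7.6b) does not exist for the waitlist arm. Women with hip or knee symptoms therefore cannot be identified from these sources in all three arms.

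**The case against.** The strongest reply is that the wording is loose rather than wrong. Appendix 19.2 acknowledges generalized use of the WOMAC, rheumatoid arthritis included, and an any-joint stem suits that use. Most pain and function items concern the legs in any case. The same form is used in every arm, so randomization protects the comparison. The WOMAC is one of twelve lettered secondary items, and leg function is also measured separately by the Timed Get Up and Go test.

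Most of this stands, and it limits the size of the point. It does not remove it. If generalized use was intended, 1.2b and 10.2b carry the wrong label. The reply also has no answer for the stiffness subscale, where no item points to the legs.

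Several stronger readings are tempting, and the documents do not support them:

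- A reader might infer that other-joint symptoms are always scored, or that a WOMAC difference could come wholly from the hands, shoulders or back. For pain and function the item content makes that implausible. Such symptoms can be scored on some items, and that is all the form shows.
- A reader might infer that the hand endpoint in 1.2c is compromised too. It is not, because every M-SACRAH section is tied to the finger joints.
- Section 15.2b tells patients to report all symptoms, which might be taken as inviting answers about any joint. That sentence concerns cause (whether or not related to the cancer or its treatment) and not body site.
- A reader might infer that many participants have no hip or knee symptoms. The survey in the Background reports only that over 50% of affected women had symptoms in the hands and/or knees. It gives no hip figure and no hands-only figure, so the frequency is unknown.

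**Conclusion.** The mismatch is real and nothing in the protocol resolves it. Followed as written, the plan would report an any-joint stiffness score as hip and knee stiffness (20 of 20 points open). It would report a partly mixed score for pain (20 of 50) and for function (20 to 70 of 170, depending on how the items are read).

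Two things are assumed: the item sorting above, and that patients answer the stems as printed. How many points actually come from other joints cannot be estimated from the documents.

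The primary endpoint, its alpha and sample size, the validity of the between-arm comparison and the M-SACRAH endpoint are untouched. The consequence is confined to interpretation: a WOMAC difference, above all in stiffness, should not be called hip/knee-specific.

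**What to change.** Settle this before data collection, because answers given to a general question cannot be assigned to a joint afterwards. There are two options.

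1. **Anchor the form.** Name the hips and knees in the three stems of Form #33579, as the M-SACRAH form names the finger joints. This means three changed sentences and no added visits or patients. The drawback is a possible loss of comparability with the source instrument or with the form used in the pilot trial. The documents show neither wording, so check both first.
2. **Keep the form and change the label.** If the wording must stay, delete the reference to hips and knees from 1.2b and 10.2b and bring the label in Appendix 19.2 into line. Describe the result as a general joint-symptom WOMAC score, consistent with the generalized use that the appendix notes, and make no hip/knee-specific claim. This costs a few words and gives up the site-specific reading.
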